#### **4.6.1 HIVIS 03**

The preparation for the continued phase I/II trial in Tanzania, HIVIS 03, has been successfully completed and the study is now fully enrolled with the required 60 volunteers, all of them Police Officers. The volunteers are of less than 40 years of age, HIV negative and generally healthy at recruitment. This is a randomized, placebo controlled trial with DNA priming and MVA boosting and preliminary results have shown excellent safety, and that the level of immunogenicity after the DNA prime alone could indeed be better than that found among the Swedish volunteers in HIVIS01 [38]. The HIVIS03 study is still blinded, and follow up of volunteers is continuing. All 50 eligible volunteers have received the three DNA injections and one booster MVA injection. The vaccines and delivery methods were well tolerated and not probably or definitely related to any grade 3 or 4 adverse events. Although the study is still blinded the immunogenicity results are similar to, or better than, those obtained in HIVIS01/02. Out of 59 vaccinees who received 3 DNA/placebo, 23 (39%) had HIV-specific IFN-gamma ELISPOT responses. On the other hand, 34 (68%) of 50 volunteers who received a MVA/Placebo boost after DNA/placebo priming had HIV-specific IFN-gamma ELISPOT responses two weeks after the boost. One third got placebo. The study is still blinded.

The continued conduct of this trial will ensure the sustainability of the whole trial organization at the Dar es Salaam site. The current programme is limited to a short follow-up after a single MVA boost, which is clearly insufficient to properly evaluate strength and durability of the immune response. The vaccine producer, WRAIR, has decided to donate further immunogens to enable a continuation with a second boost, which is currently ongoing.

#### **4.6.2 Cohort capacity building**

Multiple cohorts for phase IIB and III studies will soon be needed in many places in Africa. We have worked for many years to develop such cohorts. However, only in the context of real trials will the efforts be tested to actually be ready to perform such trials. It is furthermore very difficult to maintain the cohorts and the supporting mechanisms without the presence of ongoing trials. Such a cohort among Police Officers is currently maintained in Dar es Salaam and serves as the basis for the recruitment for the ongoing HIV vaccine trial, HIVIS 03. This cohort must be maintained and further developed in the context of a future phase II HIV vaccine trial.

In Mbeya, preparations for HIV vaccine evaluations started in 1999 with the establishment of two major cohorts which included a high-risk cohort of 600 bar workers (HISIS) and a general population cohort of 3000 adults (CODE). In 2006 a third, even larger cohort (EMINI) of 18000 individuals (above the age of 6 months) was initiated. Follow-up intervals are different in each of the cohorts. While bar workers from the HISIS cohort were followed up every 3 months, CODE participants were followed up every 6 months and EMINI participants are followed up once a year. These cohorts do not only provide detailed incidence rates and therefore allow precise planning of future vaccine trials, but also have created trust in potential vaccine populations between researchers and participants.

#### **4.6.3 Police Officers Cohort in Dar es Salaam**

The incidence and prevalence of HIV was investigated in 2,850 police officers in 1994-96 in the TANSWED programme, as mentioned above. It proved feasible to work ethically in this hierarchical group and the incidence of 1.96% together with a low turnover of personnel indicated that this group represented a potential HIV vaccine phase III cohort. Good relations have been maintained with the cohort since then and it was again approached in 2004 to prepare for a new round of incidence studies, this time coupled with questions about HIV vaccine acceptability. In the process a core group in the police force interested in working against HIV transmission was identified. This group now consists of more than 400 police officers that have been further trained to serve as the primary recruiting ground for further phase I and II studies and to facilitate future phase III HIV vaccine studies in the Police

cohort. On-going socio-behavioral studies on various aspects related to HIV and participation in HIV vaccine trials are expected to yield valuable information for the sustenance of this cohort as well as elucidation of factors that may facilitate or impede recruitment and retention of volunteers for HIV vaccine trials from the PO cohort as well as from the general public if there will be a need to do so.

#### **4.6.4 Ongoing or planned HIV vaccine and cohort studies in Dar es Salaam**

At the Dar es Salaam site the on-going HIVIS-03 (or WP-1 of TaMoVaC-01) study is now administering 2nd dose of MVA/placebo. This is a natural transition to the present study drawing on the existing resources. It is also envisaged that additional staff will be recruited as the need arise. The site will also be involved in cohort and cross sectional studies along the lines of HIV vaccine trials. These are expected to be supported through a grant application to Sida/SAREC. Recently an additional grant has been approved by the EDCTP for continued HIV vaccine studies of the HIVIS DNA and MVA-CMDR in Tanzania and Mozambique.

#### **4.7 Preliminary work on HIV vaccine trials and HIV cohorts in Mbeya**

MMRP had been involved in past HIV vaccine and cohort trials and has established an experienced study clinic, community outreach team, pharmacy and laboratories. The MMRP labs include a clinical laboratory (hematology, clinical chemistry, serology, CD4 count analysis, HIV testing and HIV RNA) as well as an immunological lab which has established FACScanto flow cytometry, ICS and ELISPOT assays throughout various studies. Both labs have been accredited by the College of American Pathologists (CAP) and participate in external QA/QC programs with UKNequas and CAP and follow therefore the highest standard of quality control and validation which is audited and monitored yearly by independent consultants. The MMRP labs have been recognized as one of the national reference laboratories. All lab staff members are GCLP trained and repeat training is performed every other year.

##### **4.7.1 HIV cohorts**

At MMRP three cohorts have been or are currently under observation, with a fourth cohort study being in the initiation process:

**HISIS** is a high-risk cohort of bar workers that has a cumulative HIV incidence of 7% over 3 years (14% first year, 5% and 3% second and third year, respectively). It has maintained in this difficult environment a high follow up rate of above 70% after 4 years [10, 39-41].

**CODE** is a general population cohort with 3000 individuals in Mbeya town and surrounding rural areas. Here, specific subgroups, such as young adults between the age of 18 and 25 have been identified to have the highest risk of HIV acquisition, with an HIV incidence of 3.2% and 2.3% for women and men.

The **EMINI** cohort consisting of 18,000 individuals has been established in 9 geographic distinct areas of Mbeya in preparation for large-scale phase III and IV trials.

**RV217** is a study funded by USMHRP and is currently in the process of being initiated. In this cohort bar workers will be recruited to assess the HIV incidence and retention rate of the risk group to be included in HIV vaccine trials.

These cohorts thus form a solid base for the recruitment of volunteers for the proposed phase II trial and for future phase IIB/III cohorts. The trial will also strengthen the community activities, the clinical trial organization and ensure that laboratory capacity is strengthened and continuously kept up to highest international standard.

##### **4.7.2 Phase I/II HIV vaccine trial in Mbeya**

MMRP participated in the multi-country (Tanzania, Kenya, Uganda) RV172: A Phase I/II Clinical Trial to Evaluate the Safety and Immunogenicity of a multiclade HIV-1 DNA Plasmid Vaccine, VRC-HIVDNA016-00-VP, Boosted by a multiclade HIV-1 Recombinant ADENOVIRUS-5 Vector Vaccine, VRC-HIVADV014-00-VP, in HIV uninfected adult volunteers in East Africa. The study was sponsored by DAIDS/NIH and conducted by the U.S. Military HIV Research Program (USMHRP). Enrollment for RV 172 began in May 2006

and ended in late October 2006. Overall 324 were enrolled in the study. In Mbeya 491 volunteers from the general population were briefed, 279 were screened and 60 participants were finally enrolled in the study. The study was conducted throughout 14 consecutive visits including 4 vaccination visits (3 DNA prime, 1 Ad5 boost vaccination). All vaccinations were completed at all RV 172 sites in April 2007 and all follow-up visits were completed in October 2007. No safety concerns for acute reactogenicity or adverse events have been recognized. The study has shown excellent immunogenicity for HIV antigens. Overall, 63% of vaccine volunteers receiving vaccine have shown a positive  $\gamma$  - IFN ELISpot response using cryopreserved cells. Response rates of up to 85% have been observed at sites employing fresh cells for this assay and the ICS assay [42-43]. During the study, one HIV infection was observed within the RV 172 volunteers, and 3 further HIV infections were detected after study completion.

#### **4.7.3 Ongoing or planned HIV vaccine and cohort studies in Mbeya**

Phase I HIV vaccine studies apart from the TaMoVac 1 study are planned in Mbeya including the HIV/DAIDS funded RV262 and the EDCTP AfreVac study. Both studies might start in 2010 and are currently in the process of protocol development. A larger HIV incidence and prevalence study (RV217) in an HIV high risk population is under ethical review and is expected to start in 2009. The RV172 vaccine trial shall be amended for safety and immunogenicity follow-up and is currently under ethical review to start in 2009. The site is capable and will be prepared to conduct these studies in parallel in respect to administrative, recruitment, outreach, clinical and laboratory activities. Mbeya is part of the approved EDCTP grant mentioned above.

A unique feature of the HIVIS 01/02 and HIVIS 03 trials is the separation of the injection of the *gag* and *env* containing pools to different arms. This was based on a superiority of this modality to a combination of all plasmids in mouse models. It would however be much more practical if all plasmids could be combined as proposed in this study.

Furthermore the project is part of a larger programme funded by the EDCTP to improve North-South collaboration in HIV vaccine trials, improve the capacity for future HIV vaccine trials in MUHAS, MMRP and Tanzania in general, through better networking of the involved institutions and to provide information as a basis for future HIV vaccine trials in Tanzania and Mozambique.

## **5 STUDY OBJECTIVES**

The objectives of the current proposal are as follows:

### **5.1 Primary objectives**

1. Determine safety of the DNA vaccine developed at Karolinska Institutet/SMI (HIVIS-DNA) at a dose of 600 µg or 1000 µg delivered i.d in combination with MVA-CMDR boost i.m
2. Determine immunogenicity of HIVIS-DNA at a dose of 600 µg or 1000 µg delivered i.d in combination with MVA-CMDR boost i.m.

### **5.2 Secondary objectives**

1. Compare immunogenicity of KI-DNA at a dose of 600 µg given as combined plasmid pools or separate plasmid pools i.d in combination with MVA-CMDR boost i.m.
2. To build expertise and capability in evaluating HIV-1 vaccine candidates in Tanzania.

## **6 METHODOLOGY**

### **6.1 Study design**

This is a randomized, controlled, double blinded study with regard to placebo/vaccine but not group.

### **6.2 Study setting**

The clinical sites will be MNH/MUHAS in Dar es Salaam and Mbeya Medical Research Programme (MMRP) in Mbeya, TANZANIA.

Laboratory tests will be performed at:

1. the Department of Microbiology and Immunology, MUHAS, Dar es Salaam,
2. the main and immunological laboratories of the Mbeya Medical Research Programme, Mbeya
3. the Swedish Institute for Infectious Disease Control, Stockholm, SWEDEN

Additional studies may be performed at:

4. The Walter Reed Army Institute of Research (WRAIR), USA
5. The Imperial College (IC), London, UK

### **6.3 Duration of study**

The recruitment and enrolment period is planned to be 12 months. The volunteers will be monitored through week 24 after the last injection ie a total of 70 weeks.

### **6.4 Study volunteers**

Primarily, volunteers will be recruited in Dar es Salaam from the Police force with whom there has been extensive prior contact for the last 10 years. Additionally volunteers will also

be recruited from the Prison force. Volunteers from the general public including young adults attending the Infectious Disease Clinic (IDC) who would have been assessed by the clinical team regarding their availability for long-term follow up will also be invited.

In Mbeya healthy volunteers will be recruited from the Mbeya urban environment. MMRP has developed over the years throughout the past cohort studies a well-established relationship to the communities and community leaders of various areas in the Mbeya region.

The study will consist of 120 healthy volunteers, of whom no less than 30 will be females found to HIV negative in the screening process and be at low risk for HIV infection.

Differential recruitment will be accommodated in case a site is not able to recruit the 60 volunteers or is unable to recruit the 15 females in the specified time of enrolment

## 6.5 Study groups

The study will have six Groups of DNA injections as follows; All followed by MVA boosts.

| Group | Number of Volunteers | DNA immunization weeks 0, 4 and 12    | MVA boost weeks 30 and 46       |
|-------|----------------------|---------------------------------------|---------------------------------|
| IA    | 36                   | 600 µg i.d (combined plasmid pools)   | MVA, at 10  pfu i.m |
| IB    | 4                    | Saline 2 x 0.1ml i.d                  | Saline, im                      |
| IIA   | 36                   | 600 µg i.d (separate plasmids pools)  | MVA, at 10  pfu i.m |
| IIB   | 4                    | Saline 2 x 0.1 ml i.d                 | Saline, im                      |
| IIIA  | 36                   | 1000 µg i.d (separate plasmids pools) | MVA, at 10  pfu i.m |
| IIIB  | 4                    | Saline 5 x 0.1 ml i.d                 | Saline, im                      |

HIV-DNA/placebo will be given at weeks 0, 4 and 12 as i.d injections with the Biojector 2000 device in the skin over the deltoid muscles.

| Group | Left Arm                                                                   | Right Arm                                                               |
|-------|----------------------------------------------------------------------------|-------------------------------------------------------------------------|
| I     | 1 injection id of 0.1 ml of 3mg/ml [300µg] Pool 1 and 2 (env/gag) combined | 1 injection id of 0.1 ml 3mg/ml [300µg] Pool 1 and 2 (env/gag) combined |
| II    | 1 injection id of 0.1 ml 3mg/ml [300µg] Pool 1 (env)                       | 1 injection id of 0.1 ml 3mg/ml [300µg] Pool 2 (gag)                    |
| III   | 3 injections id of 0.1 ml of 2mg/ml [600µg] Pool 1 (env)                   | 2 injections id of 0.1 ml of 2mg/ml [400µg] Pool 2 (gag)                |

Two HIV-MVA/placebo boost i.m. injections will be given at 18 and 34 weeks after the last (third) DNA/placebo priming injection at 10^8 pfu in the deltoid muscle.

## 6.6 Randomization procedure

Block randomization in blocks of 10 with a ratio of 9 vaccine recipients to a single placebo will be used with equal distribution among the two sites.

## 6.7 Inclusion criteria

- Age: 18 to 40 years
- Willing to undergo counseling and HIV testing
- Have a negative antigen/antibody ELISA for HIV infection
- Able to give informed consent
- Satisfactory completion of an assessment of understanding prior to enrolment defined as 89% correct answers after three opportunities to take test.
- Basic abilities to read and write.
- Resident in Dar es Salaam or Mbeya, and willing to remain so for the duration of the study
- At low risk of HIV infection, defined as the absence of an identifiable risk factor/ behavior (Their presence is therefore an exclusion criteria):
  - sexual partner with HIV

- sexual partner with unknown HIV serostatus who is also unwilling to use protective condoms consistently in all sexual relations
  - sexual partner is known to be at high risk for HIV
  - more than one sexual partner in the last 6 months
  - history of being an alcoholic [as medically defined or more than 35 units /week]
  - history of STI within past 6 months.
9. Verbal assurances that adequate birth control measures are used not to conceive/father a child during the study and up to 6 months after the last vaccine injection
  10. Women shall have a negative urinary pregnancy test
  11. Be willing to practice safe sex for the duration of the study to avoid sexually transmitted infections including HIV.
  12. Good health as determined by medical history, physical examination, clinical judgment and by key laboratory parameters as judged by the study physician.

Reference ranges will be in accordance with data generated at MUHAS for the Dar es Salaam site, and that generated at Mbeya (MMRP) for the Mbeya site. Exclusion by presence of Diabetes mellitus will be based on the DAIDS Table for Lab Criteria cut-off value of a Fasting Blood Glucose  $\geq 6.11$  mmol/L if random Blood Glucose is  $\geq 6.44$  mmol/L (Grade 1 Toxicity). Local reference ranges will be use if the DAIDS Table for Lab Criteria refers to upper limit of normal (ULN), e.g. liver enzymes, creatinine, bilirubin) or lower limit of normal, e.g. albumin (LLN). For hematology and urine analysis results of the DAIDS toxicity table criteria will be applicable.

- *Hb  $>10.5$  g/dl*
- *White blood cell count  $>13,300/\text{mm}^3$*
- *Neutrophils  $>1,200/\text{mm}^3$*
- *Lymphocytes  $>1.0/\text{mm}^3$*
- *Platelets  $>120,000/\text{mm}^3$*
- *Random Blood Glucose  $<6.44$  mmol/L; if elevated, then a Fasting Blood Glucose  $<6.11$  mmol/L*
- *Bilirubin  $<1.25 \times \text{uln}$  (DAIDS  $<1.1$ )*
- *ALT  $<1.25 \times \text{uln}$*
- *Creatinine  $<1.25 \times \text{uln}$  (DAIDS  $<1.1$ )*
- *Urine dipstick for protein and blood: negative or trace. (If either is  $\geq 1+$ , obtain complete urinalysis (UA). If microscopic UA confirms evidence of hematuria or if proteinuria  $\geq 1+$  (with a protein/creatinine ratio  $< 45\text{mg}/\text{mmol}$ ), the volunteer is ineligible).*

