Upon this information about the trial and the informed consent procedures, consenting volunteers will be requested to successfully pass a test of understanding (**Appendix 5, CRF 1-I**) with at least 90% of correct answers with the possibility of maximum 3 repeated attempts.

Demographic data and participant's contact information will be collected and recorded (CRF 5-I).

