#### **8.1.5 Blood and urine collection**

Blood will be collected using a sterile needle, usually from the ante-cubital fossa, according to the SOP's and the visit schedule and transported to the appropriate laboratories. Urine will be collected into a sterile container and tested by a member of the clinical team according to trial specific SOP's. Urine dipsticks and pregnancy test will be performed at the clinic. If urine dipsticks indicate abnormal results ( $\geq 1+$ ) urine will be transferred to the labs for microscopic examination and if indicated for culture and sensitivity. The volunteer will as well be reviewed to rule out other systemic conditions that can result into abnormal urine results such as proteinuria. In cases with confirmed proteinuria of unclear etiology a quantitative/qualitative urine protein investigation can be ordered at the referral laboratories in Dar es Salaam. Determination of Protein/Creatinine Ratio by comparing the concentration of protein in the urine to the creatinine\_level in a spot urine sample may be performed and in so doing a Protein:creatinine ratio  $>45$  mg/mmol would be considered to indicate presence of proteinuria. It should be noted that the provision of expedited cold chain transport of samples for not available lab investigations from Mbeya to Dar es Salaam is possible.

All samples for routine hematology, clinical chemistry and other investigations will be labeled appropriately with the full study volunteer identity. Samples that will be analyzed after freezing shall be prepared, labeled, and stored at the appropriate temperature. Specimens that are shipped will be correctly prepared, labeled, and kept at the correct temperature.

The total estimated volume of blood to be collected at different time points is shown on the investigations flow chart for each scheduled visit (**see Appendix 3**). All biological samples to

be analyzed by the research laboratory will be collected and processed according to institutional guidelines and regulations regarding biobanks. All samples sent to the appropriate laboratories at MUHAS and MMRP will be labeled appropriately.

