## Appendix 6A: TaMoVac I Risk Assessment of Volunteers (English)

We will ask you about your sexual experience. You do not have to answer any questions that make you feel uncomfortable however; this may affect your eligibility and opportunity to participate in this trial. All your answers will be treated confidentially. No one will be allowed to disclose our answers outside our research group.

1. Have you ever had sexual intercourse?
  - a. ☐ Yes
  - b. ☐ Never had (*jump to questions 7, 8, 9 and 10*)
2. How many sexual partners have you had during the past six months?
  - a. ☐ ≤ Two (2)
  - b. ☐ More than Two
3. Are you in a relationship with an HIV infected partner?
  - a. ☐ Yes
  - b. ☐ No
  - c. ☐ I don't know
4. Among the people you have had sex with, are there any individuals who you knew or suspected were HIV positive in the past 6 months?
  - a. ☐ Yes (Knew or Suspected)
  - b. ☐ No
5. In the past 6 months, how often have you had sexual intercourse with prostitutes or exchanged sex for money, goods or services?
  - a. ☐ Have NOT had sexual intercourse with prostitutes in the past 6 months
  - b. ☐ Have NOT exchanged sex for money, goods or serviced in the past 6 months
  - c. ☐ Have had sexual intercourse with prostitutes in the past 6 months
  - d. ☐ Have exchanged sex for money, goods or serviced in the past 6 months
6. During the past 6 months, have you used condoms during sexual intercourse with casual partners?
  - a. ☐ Always
  - b. ☐ Sometimes
  - c. ☐ Seldom or Never
7. In the past 6 months, have you been diagnosed with a sexually transmitted disease?
  - a. ☐ Yes
  - b. ☐ No
8. In the past 6 months, have you had any of the following symptoms?
  - a. ☐ Genital sores
  - b. ☐ Discharge from vagina with itching or burning
  - c. ☐ Pus discharge from penis
  - d. ☐ Frequent, difficult, or painful urination
  - e. ☐ None of the above

9. Are you regular drinking alcohol defined as >21 units per week (male), >14 units per week (female) → 1 units = 1 beer or 1 glass of wine or measure of strong alcohol.

- a. ☐ Yes
- b. ☐ No

10. Have you ever used intravenous recreational drugs?

- a. ☐ Yes
- b. ☐ No

The use of this assessment tool is designed to facilitate a discussion with the patient and inform clinical judgment about volunteer risk. It is not a validated instrument and seeks to briefly identify high-risk behaviors which would be grounds for excluding a volunteer.

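### Several eligibility thresholds in section 6.7 are untenable as written or conflict with section 8.1 and the screening questionnaire

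*Protocol*

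**What the plan says.** The health criterion in section 6.7 ends with a list of values to be met. Haemoglobin, neutrophils and platelets carry lower bounds; glucose, bilirubin, ALT and creatinine carry upper bounds. The same list contains "White blood cell count $>13,300/\text{mm}^3" and "Lymphocytes $>1.0/\text{mm}^3". Section 6.7 also says that the DAIDS table (Appendix 9) applies to haematology and urine results.

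On urine, section 6.7 treats confirmed proteinuria of 1+ or more as disqualifying in these words: "with a protein/creatinine ratio $< 45\text{mg}/\text{mmol}$ ), the volunteer is ineligible". Section 8.1.5 says that a ratio above 45 "mg/mmol would be considered to indicate presence of proteinuria".

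On HIV risk, section 6.7 excludes anyone with "more than one sexual partner in the last 6 months". Section 8.1.2 names the Appendix 6 questionnaire as the tool for assessing risk. Its question 2 asks "How many sexual partners have you had during the past six months" and gives two answers, two or fewer and more than two. The Swahili version in Appendix 6B splits at the same point.

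On the understanding test, section 6.7 sets the pass mark as "defined as 89% correct answers after three opportunities to take test". Section 8.1.1 asks for a pass "with at least 90% of correct answers". Appendix 5 scores the test out of 19.

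**The concern.** These are decision thresholds. Section 8.3 requires staff to confirm and record at enrolment that every inclusion and exclusion criterion is met, laboratory results included, and section 15 requires any departure from the protocol to be recorded and reported within two working days. A criterion that cannot sensibly be applied, or that is stated in two incompatible ways, leaves each site to choose its own reading. With two sites, the choices may differ.

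The partner question bears on safety. Section 4 says HIV infections should be avoided as a principle in an early trial of this kind, section 14.2 makes any HIV infection a Grade 4 serious adverse event, and section 16.2 pauses the study for a single Grade 4 serious adverse event judged possibly related to vaccination. The pass mark helps decide who has understood the study well enough to enter it.

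**Working it through.** The plan has no figure of its own to reproduce here. The check sets each threshold beside the text it should agree with.

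**(a) White cells.**
- Section 6.7: above 13,300/mm³ required.
- Appendix 9: the only white cell row is for decreased counts, with Grade 1 at 2,000–2,500/mm³.
- Ratio: 13,300 / 2,500 = 5.32.
- Read literally, everyone at or below 13,300/mm³ is ineligible, including every count that Appendix 9 leaves ungraded between 2,500 and 13,300/mm³.

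**(b) Lymphocytes.**
- Section 6.7: above 1.0/mm³ required.
- Appendix 9 (HIV negative): Grade 1 at 600–650/mm³, Grade 4 below 350/mm³.
- Ratios: 650 / 1.0 = 650 and 350 / 1.0 = 350.
- One litre is 10⁶ mm³, so 1.0 × 10⁹/L = 1,000/mm³. The entry fits a unit slip by a factor of 1,000.
- As written, the line does not bind.

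**(c) Protein/creatinine ratio.**
- Section 6.7: ineligibility is tied to a ratio below 45 mg/mmol.
- Section 8.1.5: proteinuria is indicated by a ratio above 45 mg/mmol.
- A volunteer with confirmed 1+ protein and a ratio above 45 has proteinuria under 8.1.5 but falls outside the ineligibility clause in 6.7. With a ratio below 45, the reverse holds.

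**(d) Sexual partners in six months.**

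| Partners | Criterion in 6.7 | Answer in Appendix 6 |
|---|---|---|
| 1 | not excluded | two or fewer |
| 2 | excluded | two or fewer |
| 3 or more | excluded | more than two |

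The form and the criterion disagree at exactly two partners, and the answer does not separate one partner from two.

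**(e) Understanding test.**
- 16/19 = 84.2%: fails both rules.
- 17/19 = 89.5%: passes 89%, fails 90%.
- 18/19 = 94.7%: passes both.

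The minimum is 17 correct under section 6.7 and 18 under section 8.1.1.

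**The case against.** Several points on the other side are fair. The health criterion leaves laboratory parameters to the study physician's judgement, and no physician would enforce the white cell line as printed. For lymphocytes, the DAIDS table is said to apply anyway, so low counts are not left unguarded. The protein/creatinine ratio is optional in section 8.1.5 and follows a positive dipstick, so few volunteers would reach it. Appendix 6 describes the questionnaire as an aid to discussion and not a validated instrument, and the criteria are checked again at visits 2 and 3. The two pass marks differ by one question, and understanding is re-checked at both of those visits.

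All of this softens the practical effect. It does not tell a site what the written rule is, and a discussion aid meant to bring out excluding behaviour should be able to record it.

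A reader might go further than the documents allow, in five ways:
- That a stated share of healthy volunteers would fail the white cell line. The protocol gives no distribution of counts.
- That these figures are printed on the eligibility form. The form is named but its content is not shown.
- That the white cell sign is simply reversed. The other blood count lines are all lower bounds, so the number may equally be at fault.
- That the lymphocyte line admits or rejects the wrong people. It only fails to bind.
- That a volunteer with two partners cannot be found. Discussion may find one; the form cannot record it.

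The disputed entries in (a) to (c) turn on signs, digits and units, which are easily damaged when a file is converted. The sponsor should check them against its source document.

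**Conclusion.** The point holds for all five thresholds as written, with unequal weight. The white cell line is untenable as a minimum, at 5.3 times the top of the only graded white cell range. The ratio rule contradicts itself between sections 6.7 and 8.1.5. The partner question misses the excluding value of exactly two. The lymphocyte line is non-binding, 350 times below the Grade 4 limit, and the pass mark differs by one correct answer in 19.

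Taken together, written eligibility cannot be applied literally and consistently, and this should be corrected. The conclusion rests only on comparing the protocol with itself, assuming that the printed signs and units are those of the source file. It does not depend on how common any laboratory value is. Randomisation, endpoints, sample size and analysis are unaffected.

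**What to change.** - The sponsor should reconcile and restate the intended white cell and lymphocyte limits (sign, number and unit) against Appendix 9 and the local reference ranges. No limit is proposed here.
- Reconcile sections 6.7 and 8.1.5 so that both state the same direction for the protein/creatinine ratio.
- Align the answers to question 2 of Appendix 6, in English and Swahili, with the criterion in section 6.7. If that criterion stands, 0 / 1 / 2 or more would do it.
- State one pass mark for the understanding test, as a number correct out of 19, in sections 6.7 and 8.1.1.

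The cost is amendment text, a revised question in two languages, and a check of any case report form that repeats these thresholds. No procedure, visit or sample is added.
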